## Abstract

**Introduction:**

Circadian rhythms (CR) regulate daily cycles in behavior, physiology and molecular processes. CRs are endogenous and vary across individuals. Seasonal changes can influence CR. Accordingly, rhythms with different characteristics (amplitude, phase) are depicted during the summer months, as compared to winter. Increasing evidence points to an influence of circadian regulation on physical performance. Here, we aim to obtain a comprehensive circadian gene expression profile for physically active individuals, which can potentially be used for the identification of optimal time intervals for physical exercise.

**Methods and analysis:**

To explore these different aspects, we propose a study where we will carry out a molecular analysis of CR by measuring the expression of specific clock and clock-controlled genes, based on a non-invasive approach using RNA extracted from saliva in physically active, healthy participants. We will collect data across two seasons and use computational algorithms to integrate the molecular data with hormonal data (cortisol and melatonin), and generate a profile of CR in healthy individuals of different sex and age groups. Finally, we will use computational tools to predict optimal time intervals for physical performance based on the above-described data, thereby retrieving valuable data on the circadian clock as a key factor for health maintenance and optimization.

## Introduction

In mammals, the time of physiological and cellular processes is regulated by an endogenous time-generating mechanism—the circadian clock, which enables optimal adaptation to external cues such as the day/night cycles [1]. The circadian system consists of a central pacemaker, located in the suprachiasmatic nucleus that synchronizes peripheral oscillators in each cell of the body. Circadian rhythms (CR) are 24-hour oscillations found in more than 40% of all protein coding genes across mammalian tissues [2]. CR are generated by a network of regulatory elements, the core-clock genes, including *BMAL1* (Basic Helix-Loop-Helix ARNT Like 1, also known as *ARNTL)*, *NR1D1*, *2* (Nuclear Receptor Subfamily 1 Group D Member 1, 2), *ROR A*, *B*, *C* (RAR-Related Orphan Nuclear Receptor A, B, C), *PER1*, *2*, *3* (Period 1, 2, 3) and *CRY1*, *2* (Cryptochrome 1, 2), interconnected via transcriptional/ translational feedback loops [3]. Both the core-clock genes, as well as its targets, the so-called clock-controlled genes (CCGs), are involved in crucial processes in the organism, including sleep/wake cycles, mood, memory formation, metabolism, and immunity [4–6].

Circadian dysregulation may occur as a result of life style factors, such as constant shift work [7, 8], or as a result of alterations in core-clock genes (due to mutations or aberrant gene expression activity) [9]. Such dysregulations are associated with several pathologies, ranging from circadian rhythm sleep disorders, under G47.20 code by International Classification of Diseases 10th Revision (ICD-10) [10], Alzheimer’s Disease and other dementias [11], Parkinson’s Disease [12], and cancer [13–15]. Hence, the study of the circadian clock in health and disease prevention is timely, and has enormous medical relevance.

The assessment of a dysregulated clock and its implication in disease requires the characterization of a healthy clock. The CR varies among individuals [16] and additional features such as sex, age or environmental influences (e.g., seasons) need to be considered. Females tend to exhibit an earlier circadian peak phase as compared to males, and previous reports showed a different therapeutic impact among females and males in colorectal cancer patients treated under chrono-modulated therapy regimes [17, 18]. Aging may also influence the CR resulting in dampening of the circadian amplitude, an advance of circadian phase, or result in gain or loss of rhythmic circadian expression [19–24]. Recent transcriptomics studies further revealed differential regulation of circadian gene expression between middle/older aged individuals, and younger adults [23, 25]. CR also fluctuate as a result of seasonal changes in light exposure as measured in sleep onset/offset times and duration [26, 27].

Monitoring the CR is possible via different methods, depending on the particular aim of the study, ranging from questionnaires to hormonal assessment via cortisol or dim-light melatonin onset [28–30]. These methods however, do not assess the molecular clock, or are time consuming and require medical assistance. Thus, a user-friendly and non-invasive method to assess the CR is advantageous. In this regard, the use of saliva-based methods, like TimeTeller^®^ [31] used in this study allows to assess gene expression profiles [31–33], and can be used to monitor the CR in humans [31–34]. The system-level regulation of the clock imposes optimal time frames for daily activities. Published data indicate an influence of circadian regulation on the physical performance for example, for professional athletes [35–37].

In this study, we aim to characterize and monitor the circadian clock with respect to sex in healthy individuals for different age groups, including teenagers (≤18 years old); younger adults (18–40 years old) and older (>40–60 years old individuals across the year via measurement of core-clock and CCGs in saliva samples. We will analyze participants with respect to additional factors based on characteristics like the chronotype, mid-sleep time, and activity scores, or frequency of sick-related absence at work, to explore a potential correlation among these different factors and gene expression changes of circadian genes. In addition, to characterize a healthy CR, we aim to combine such data to obtain a comprehensive profile of optimal performance for participants, which can potentially be generalized to other individuals with similar CR profiles. We will complement our analysis with other physiological parameters including hormonal data from melatonin, which has been reported to depict high values during the night thereby promoting sleep, and cortisol with high levels in the morning, promoting alertness. Given the increase usage of wearables and its potential for assessment of daily oscillations [38], we will also collect smart tracker data and monitor parameters such as activity, for each participant and search for significant correlations with the gene expression data.

## Materials and methods

### Aim of the study

The planned study aims at the measurement of circadian gene expression (by quantification of RNA) from saliva to characterize CR among different individuals, and compare the difference in CR in subgroups with respect to sex, age and across seasons.

### Study design

This is a prospective, monocentric, non-interventional observational study, which uses data collected from healthy and physically active participants in Germany **(Fig 1)**. Saliva samples will be collected by the participants themselves at home. For the analysis of potential seasonal variations, samples are grouped into a spring/summer batch and autumn/winter batch. Two rounds of saliva collection will take place between April-September 2022/2023 as spring/summer batch; and two rounds in October-March 2022/2023 (based on DST/standard time change date), as autumn/winter batch. In total four sampling rounds per person, till the end of 2023, are aimed to be collected. For each sampling round, 8 saliva samples per sampling kit, at four time points per day, should be collected during two consecutive days **(Fig 1)**.

**Fig 1 pone.0293226.g001:**
[figure not shown]
Study design flow chart. **A.** Participants meeting the study inclusion criteria will be enrolled in the study. Participants are requested to collect saliva in total for four rounds at different times of the year. Enrolled participants will fill digital forms and carry out hormonal assessment and activity tracking as indicated. **B.** Saliva sampling is carried out according to the depicted scheme. Per round of saliva sample collection, participants collect saliva four times per day, during two consecutive days (in total four rounds of saliva-sampling for CR expression will be collected per participant).

### Objectives

#### Primary objective

The primary objective of the study is the molecular characterization of the individual CR in physically active, healthy volunteers (see ‘*Participant Recruitment’* section for further details) through the use of RNA extracted from biological samples (saliva), and the development of a characteristic CR profile in specific subgroups defined by biological sex, age and seasons. Although the CR varies between individuals, according to our sample size estimation, the population that is physically active and without any chronic disease at the time of sampling may therefore represent a healthy control group of participants. Comparison of variation coefficient between CR of females vs males, detection of the seasonal influence and impact of age on the CR will be evaluated.

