#### Sample size estimation

Sample size calculation was performed based on *BMAL1* gene expression data from our previous work [34] assuming that all measurements follow a sinusoidal wave function $y_{i}=A\;sin\;(\omega (t_{i}+\phi ))+M+\varepsilon_{i}$, 1 ≤ i ≤ n whereby n is the total number of samples, $\omega =\frac{2\pi }{Period}$ the frequency of the sinusoidal wave, φ the phase shift, M the rhythm-adjusted mean (MESOR), and t_i_ the observed Zeitgeber time. ε_i_ is the error term for sample i. We assume ε_i_ are identically and independently distributed from $\varepsilon_{i}∼N(0,\sigma^{2})$, where σ is the noise level. The null hypothesis that there is no circadian rhythmicity (H_0_ = 0) is tested against the alternative hypothesis that a circadian rhythmicity pattern exists (H_A_≠0). Rhythmicity will be tested using the F-test which compares the fitted model against a restricted model. For details see please Cornelissen [39]. The study is considered successful if rhythmicity is detected in the measured core-clock and clock-controlled genes obtained from saliva samples. To account for multiple comparisons (comparisons between gender and age subgroups and various seasons, in total up to 10 comparisons) the type I error is set to 0.005 according to the Bonferroni correction to hold the global significance level of α = 0.05. Underlying the data of our previous study [34], an amplitude (A) of 1.11 is estimated for *BMAL1* gene expression and the standard deviation of residuals (s) is 1.36, which gives an estimate of the intrinsic effect height of r = A/s = 0.82.

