#### Secondary outcome measures

Analysis of the influence of sex on the CR by comparison of CR profiles of males and females. Investigation of the seasonality of CR by collection of saliva samples during two seasons (spring/summer and fall/winter). Analysis of the influence of age on the CR by comparison of CR profiles of younger probands (age between 13 and 18 years old) and profiles of older and younger adults, considering participants between 18–39 and 40–60 years old in separate groups.

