#### Analysis for primary endpoint

Amplitude, phase and mesor of the circadian data for the subgroups according to sex, age and season will be estimated per core clock gene using cosinor (harmonic) regression. The null hypothesis that there is no circadian rhythmicity (H_0_ = 0) is tested against the alternative hypothesis that a circadian rhythmicity pattern exists (H_A_≠0). The study is considered successful if rhythmicity is detected in some of the measured genes.

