#### Analysis for secondary endpoints

Differences in CR and mean gene expression level between subgroups, with respect to sex, age, seasons and physical performance, will be evaluated by CircaCompare [57] to estimate and observe differences between CR, specific to the characteristic desired (mesor, amplitude and phase). The methodology proposed by Parsons *et al*. [57] will be used for exploratory purposes, and circadian curves will be estimated per individual and sampling round. Additionally, correlations between molecular data and physical exercise measurements, as well as for hormonal data (melatonin and cortisol) and activity data (smart-tracker) will be calculated.

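### The sex, age and season comparisons are primary in one section and secondary in others, and the 0.005 level they justify is applied only to a rhythm test that compares no groups

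*Protocol article*

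**What the plan says.** All of these statements are in the protocol article.

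- **Primary objective.** It includes "development of a characteristic CR profile in specific subgroups defined by biological sex, age and seasons". It then adds a comparison of the variation coefficient between females and males and says that "detection of the seasonal influence and impact of age on the CR will be evaluated".
- **Secondary outcome measures.** The first item is "Analysis of the influence of sex on the CR by comparison of CR profiles of males and females". Season and age follow under the same heading. The Secondary objectives section names none of the three.
- **Sample size estimation.** The type I error is set to 0.005 by Bonferroni, from a global 0.05, to allow for "comparisons between gender and age subgroups and various seasons, in total up to 10 comparisons". The ten are not listed. The test that is sized is the F-test of rhythmicity, giving 52. After 12% dropout, 59 participants are called sufficient for the planned comparisons by sex, age or season.
- **Analysis for primary endpoint.** Amplitude, phase and mesor are estimated for subgroups by sex, age and season. The only hypothesis is this: "The null hypothesis that there is no circadian rhythmicity (H_0_ = 0) is tested against the alternative hypothesis that a circadian rhythmicity pattern exists". Success is defined by rhythmicity.
- **Analysis for secondary endpoints.** The group contrasts are placed here: "Differences in CR and mean gene expression level between subgroups, with respect to sex, age, seasons and physical performance, will be evaluated by CircaCompare". No level is given. The next sentence says that the methodology of the same cited reference "will be used for exploratory purposes, and circadian curves will be estimated per individual and sampling round".

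**The concern.** A reader needs to know three things about the group contrasts: their rank among the objectives, the level at which they are tested, and whether the sample size was chosen for them. The protocol gives two ranks. It derives a level from the contrasts but attaches that level to another test. It then says that the resulting sample size covers the contrasts.

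Suppose a sex or season difference comes out with p between 0.005 and 0.05. One section would let it be reported as bearing on the primary objective. Others would make it a secondary result, with or without having missed a Bonferroni threshold. A study that detects rhythm, and so counts as successful, could also be presented as having met a primary objective whose group comparisons were never part of the success test. A null contrast could be read as adequately powered because 59 is said to be enough.

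**Working it through.** **1. Which test carries the 0.005.** Inputs from Sample size estimation: amplitude A = 1.11, residual SD s = 1.36, r = A/s = 1.11/1.36 = 0.816 (stated as 0.82), α = 0.05/10 = 0.005, power 0.8.

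The cosinor F-test has 2 and n − 3 degrees of freedom. With evenly spaced sampling (an assumption), its noncentrality is λ = n·r²/2.

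- n = 52: λ = 52 × 0.82²/2 = 52 × 0.6724/2 = 17.48. The critical F at 0.005 with 2 and 49 df is 5.915. Power is 0.800.
- n = 51: power is 0.788.

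So 52 reproduces exactly. With the unrounded r of 0.816 the answer is 53, which is immaterial. The 59 is consistent with 52 × 1.12 = 58.2, rounded up.

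**2. What that calculation contains.** It has one amplitude, one residual SD and one n. It has no second group, no allocation between groups, and no difference in mesor, amplitude or phase. It therefore says nothing about power for a sex, age or season contrast. Using 0.005 here limits false claims of rhythm, not false claims of a group difference.

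**3. What the correction does to the rhythm test.** At α = 0.05 the same formula gives n = 32 (power 0.802), and n = 52 gives power 0.961. The step from 32 to 52 comes entirely from a correction whose stated reason is a set of comparisons that this test does not make.

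**4. What the open level is worth for the contrasts.** The protocol does not list the ten comparisons, so I assume five two-sided contrasts (1 sex, 3 age pairs, 1 season) on one gene and one parameter.

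For independent tests the chance of at least one false difference is 1 − (1 − α)^5:

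- α = 0.05: 1 − 0.95^5 = 0.226
- α = 0.005: 1 − 0.995^5 = 0.025

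For correlated tests I used equicorrelated normal statistics, simulated with 40,000 runs. Numerical integration agrees within 0.003.

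| Correlation | each at 0.05 | each at 0.005 | ratio |
|---|---|---|---|
| 0 | 0.226 | 0.025 | about 9 |
| 0.5 | 0.180 | 0.021 | 8.6 |
| 0.8 | 0.126 | 0.016 | 7.9 |

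The gap is about 8- to 9-fold when compared at the same correlation.

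**The case against.** **Four incompatible statuses.** A reader might infer that the contrasts are at once primary, secondary, alpha-controlled and exploratory, and that these exclude one another. The documents do not support that. Alpha control is not a rank; a secondary contrast can be tested at a controlled level. The sentence with the exploratory label also mentions curves per individual and sampling round, and can be read as covering only those. What stands is the conflict between primary and secondary. Because the sentence cites the reference given for CircaCompare, it also leaves the role of the contrasts ambiguous.

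**No level at all.** A reader might also infer that no level exists for the contrasts. One does: Sample size estimation names them as the reason for 0.005. It is simply not carried into the section that analyses them. No section proposes 0.05 per contrast either, so that column of the table shows what is left open, not what is planned.

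**A coherent use of 0.005.** The rhythm test might be meant to run within each subgroup: 2 sexes + 3 age groups + 2 seasons = 7, which fits up to ten. The primary analysis does estimate parameters by subgroup, and so delivers the profile part of the primary objective. However, the text speaks of comparisons between subgroups, which counts against this reading. Even if it is accepted, the CircaCompare contrasts still have no level and no sample size basis.

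**Limited consequence.** The study is observational, and success depends on rhythmicity alone, so the contrasts cannot change the success decision. That is correct, and it limits the point to how group differences may be reported.

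**Conclusion.** The point holds in this form. The sex, age and season comparisons are primary under the objectives and secondary in the outcome list and the analysis section. The 0.005 they justify is applied only to the rhythm F-test. The figure of 52 is correct for that test, but it gives the contrasts no error control and does not support the statement that 59 participants are enough for them.

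The size of the open question is 13–23% against about 2% for at least one false difference. This rests on five contrasts, one gene, one parameter, and correlation between 0 and 0.8. The reproduction of 52 rests on evenly spaced sampling and r = 0.82.

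The point does not show that the rhythm test is mis-sized or that the success rule is affected. The conflict is between current sections of one document, so it is not a detail left to a separate analysis plan. It should be corrected, because the protocol itself invokes a global level and a Bonferroni correction and must say what they govern.

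**What to change.** 1. **Primary objective:** limit it to detecting and characterising rhythm, including the subgroup profiles that the primary analysis estimates. Move the between-group comparisons to the secondary objectives, matching the outcome list and analysis section. When moving the sex comparison, reconcile the quantity compared: the objective names a variation coefficient, while the analysis names mesor, amplitude and phase.
2. **Analysis for secondary endpoints:** keep the exploratory label for the per-individual, per-round curves only. Give the group contrasts one role. Either test them at 0.005 over a listed family, or present them as supportive estimates with confidence intervals and no confirmatory claim.
3. **Sample size estimation, level:** stop saying that 0.005 on the rhythm test accounts for the group comparisons. Describe it as a deliberately stricter level for the rhythm test, which keeps n = 52.
4. **Sample size estimation, participants:** state that 52 and 59 are sized for detecting rhythm and not for the sex, age or season comparisons.

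These are wording changes that need no new data or participants. The cost is that group differences can no longer be presented as primary results or as powered by the stated sample size.

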#### Secondary objectives

Using the collected activity tracker data in parallel to the saliva sampling, a correlation analysis will be carried out between CR and the activity data. An additional subgroup analysis based on the questionnaire and medical history results and gene expression changes will be carried out. For the analysis, we plan to also include data from our previous study (Basti *et al*. 2021 [34]) in which participants carried out physical activity tests at different times of the day. This data set will be used to support the development of predictors for establishment of the optimal time intervals for physical exercise.

#### Explorative objectives

Investigation of the possible association between CR and the expression of up to 800 target genes using a multiplexing system (using a nanostring nCounter SPRINT Profiler) will be performed on a subset of individuals to allow a comparison between different age groups within the cohort. The detection of the possible association between melatonin/cortisol level and the CR is an additional explorative objective.

#### Sample size estimation

Sample size calculation was performed based on *BMAL1* gene expression data from our previous work [34] assuming that all measurements follow a sinusoidal wave function $y_{i}=A\;sin\;(\omega (t_{i}+\phi ))+M+\varepsilon_{i}$, 1 ≤ i ≤ n whereby n is the total number of samples, $\omega =\frac{2\pi }{Period}$ the frequency of the sinusoidal wave, φ the phase shift, M the rhythm-adjusted mean (MESOR), and t_i_ the observed Zeitgeber time. ε_i_ is the error term for sample i. We assume ε_i_ are identically and independently distributed from $\varepsilon_{i}∼N(0,\sigma^{2})$, where σ is the noise level. The null hypothesis that there is no circadian rhythmicity (H_0_ = 0) is tested against the alternative hypothesis that a circadian rhythmicity pattern exists (H_A_≠0). Rhythmicity will be tested using the F-test which compares the fitted model against a restricted model. For details see please Cornelissen [39]. The study is considered successful if rhythmicity is detected in the measured core-clock and clock-controlled genes obtained from saliva samples. To account for multiple comparisons (comparisons between gender and age subgroups and various seasons, in total up to 10 comparisons) the type I error is set to 0.005 according to the Bonferroni correction to hold the global significance level of α = 0.05. Underlying the data of our previous study [34], an amplitude (A) of 1.11 is estimated for *BMAL1* gene expression and the standard deviation of residuals (s) is 1.36, which gives an estimate of the intrinsic effect height of r = A/s = 0.82.

In order to detect an intrinsic effect of r = 0.82 as significant at α = 0.005 and achieve a power of 0.8, a sample size of 52 is necessary (**Fig 2**). The sample size was estimated by R package CircaPower [40]. A dropout rate of 10–15% [41–44] is generally considered for calculating the sample size in clinical studies although there is no universal filter. As a compromise for potential higher dropout due to the longitudinal design of our study, we considered a dropout of 12% in our sample size estimation, and calculated a population of 59 participants to be sufficient to allow for the planned comparisons in the subset of a) females vs males or b) age groups or c) seasons. Participants will be distributed evenly for comparisons (e.g., for sample size) or appropriate statistical measures will be taken, by using statistical tests considering unequal sample size. Participants for whom there are no saliva samples collected are considered as dropout.

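### The rhythm F-test assumes independent samples and no participant term is named for the subgroup comparisons, although each person gives up to 32 samples; carried over, this makes sex and age tests too liberal

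*Protocol article*

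**What the plan says.** Sample size estimation sets out a sinusoidal model in which "n is the total number of samples". On the errors it says: "We assume ε_i_ are identically and independently distributed from" a normal distribution. It goes on: "Rhythmicity will be tested using the F-test which compares the fitted model against a restricted model". This is worded as the planned test, not only as a device for computing power. For the sex, age and season comparisons, up to ten in all, "the type I error is set to 0.005 according to the Bonferroni correction". The resulting 52 is inflated for 12% dropout and reported as 59 participants, said to suffice for those comparisons.

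Analysis for primary endpoint says that amplitude, phase and mesor for the sex, age and season subgroups "will be estimated per core clock gene using cosinor (harmonic) regression". Analysis for secondary endpoints says that subgroup differences "will be evaluated by CircaCompare [57] to estimate and observe differences between CR". It adds curves per individual and sampling round, in a sentence that describes the method as exploratory. Neither section names a participant term.

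Study design plans eight samples per round over two days. It continues: "In total four sampling rounds per person", two in each season. The Abstract, Introduction and Primary objective all say that circadian rhythms vary between individuals.

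**The concern.** Samples from one person share that person's mean level, amplitude and phase. The independence assumption therefore conflicts with both the repeated-sampling design and the study's own premise.

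Sex and age group are fixed for a person. For them the amount of independent information is set mainly by the number of people, and a pooled regression that counts each sample as new information understates the standard error. Season varies within a person, so its pooled test is affected differently.

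Sex and age differences are named outcomes, and the profiles are meant to serve as a healthy reference group. A spurious difference would be carried into later work. The Bonferroni level of 0.05/10 = 0.005 protects the family of comparisons only if each test really runs at 0.005.

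**Working it through.** **The plan's own figure.** Inputs from Sample size estimation: A = 1.11, s = 1.36, r = 0.82, alpha 0.005, power 0.80. For an F-test on 2 and n - 3 degrees of freedom with noncentrality n·r²/2, n = 52 gives power 0.800 and n = 51 gives 0.788. So 52 is reproduced, as a count of independent samples. In the design, 52 samples are 52/8 = 6.5 rounds, whereas 52 people would give 52 x 32 = 1,664 samples. The arithmetic is sound, but the unit changes from samples to participants between the formula and the conclusion.

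**Assumptions for the checks below.** 52 people, 26 of each sex, all 32 samples present, at the protocol's example times (9, 13, 17 and 21 h). Let p be the share of variance between people, q the share between rounds within a person, and 1 - p - q the rest. The document gives neither p nor q. The mesor results depend only on these shares, not on A or s.

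**Sex difference in mesor, q = 0.** With these four clock times the variance of a fitted mesor is 2σ²/n rather than σ²/n, because the night is not sampled. Per person:
- true variance: p + 2(1 - p)/32
- variance assumed by the pooled test: 2/32
- ratio: 16p + (1 - p) = 1 + 15p

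The two-sided critical value at 0.005 is 2.807. The actual error rate is 2·[1 - Φ(2.807/√ratio)].

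| p | Ratio | Actual error (formula) | Simulation, 10,000 datasets |
|---|---|---|---|
| 0 | 1.0 | 0.5% | 0.5% |
| 0.1 | 2.5 | 7.6% | 7.6% |
| 0.3 | 5.5 | 23.1% | 23.3% |

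Smaller separate simulations gave about 7% and 24%. If amplitude and phase also vary between people, the rates were 4 to 7% at p = 0.1 and 18 to 21% at p = 0.3, because the pooled residual variance grows.

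**Sex difference in rhythm.** Using person-specific cosine and sine coefficients with SD 0.3 or 0.6 (error plus intercept variance set to 1), pooled tests rejected in 4 to 8% and 25 to 27% of null datasets.

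**Season difference in mesor.** The person's level cancels. Each person has two rounds (16 samples) per season:
- true variance per person and season: q/2 + 2(1 - p - q)/16
- assumed: 2/16
- ratio: 4q + 1 - p - q = 1 - p + 3q

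| p | q | Ratio | Formula | Simulation |
|---|---|---|---|---|
| 0.1 | 0 | 0.9 | 0.3% | 0.3% |
| 0.3 | 0 | 0.7 | 0.1% | 0.1% |
| 0.3 | 0.1 | 1.0 | 0.5% | 0.5% |
| 0.1 | 0.1 | 1.2 | 1.0% | 1.1% |

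The test is conservative when 3q < p and liberal when 3q > p.

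**Rhythm F-test.** Under the stated null, with nobody rhythmic and only mesor varying (26 people, 32 samples each, 5,000 runs), the pooled test rejected in 0.50%, 0.36%, 0.02% and 0% of runs at p = 0, 0.1, 0.3 and 0.5. It rejects too often only as a test of a rhythm common to the group: 4 to 8% at coefficient SD 0.3 and 23 to 26% at SD 0.6, where individuals do have rhythms but their average vector is zero.

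**Participant-level alternative.** One cosinor fit per person, then Hotelling's T² for rhythm or a t-test on mesor, gave 0.43 to 0.65% (6,000 replicates), close to nominal. Power at r = 0.82 with 52 people was about 1.00 in every setting tried.

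**The case against.** The independence statement stands only under Sample size estimation. The analysis sections state no error structure, the details of both methods are left to cited papers, and a full analysis plan could add random effects. The protocol also has participant-level elements: its primary objective concerns individual rhythms, it calls the design longitudinal, and it plans individual curves.

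Part of this stands. For CircaCompare, independence is an inference, so the sex and age error rates are conditional. For the rhythm test it is not: the article states the model and says it will be used, so a plan with random effects would contradict it. The individual curves are tied to no group test.

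Three stronger readings are tempting, and the documents do not support them.
- *The primary rhythm test is anti-conservative.* The protocol's null is no rhythmicity. When people have rhythms without a common phase, rejecting is not an error under that null; when nobody is rhythmic and only mesor varies, the test is at or below nominal.
- *Ignoring the person always makes the season test inefficient.* That holds only if round-to-round variance is small relative to person variance.
- *A mixed model cures the shrinkage of group amplitude from scattered phases.* With common sampling times, pooled and participant-level analyses both estimate the mean cosine and sine vector. Its amplitude shrinks by 1 - exp[-(2π·SD/24)²/2], or 13%, 27% and 42% at phase SDs of 2, 3 and 4 h, under either. That is a choice of estimand.

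**Conclusion.** The point holds in conditional form. The plan states an independent-error test with n in samples and then applies cosinor methods to subgroups of repeatedly sampled people with no participant term. If the comparisons follow that assumption, sex and age tests are anti-conservative. With only modest between-person variance (p = 0.1 and no other person effects), one sex comparison of mesor alone runs at 7 to 8%, more than the 5% meant for all ten comparisons together. The figures are for sex with a 26 to 26 split; the age comparison fails by the same mechanism but was not sized. With no between-person variation the distortion vanishes, but the protocol itself says that rhythms vary between people. The season test is miscalibrated in a direction the documents do not settle. The 52 is not an arithmetic error, and detection of the overall rhythm is not under threat.

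**What to change.** Replace the independent-error model, for the rhythm test and for the sex, age and season comparisons, with one of these per gene:
- a mixed-effects cosinor with participant random mesor, cosine and sine terms, and round nested in participant; or
- a two-stage population cosinor, fitting each participant and then testing the participant-level estimates across people.

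Treat season as a within-participant contrast. Say whether 52 counts samples or participants. If individual amplitude is the quantity of interest, compare participant-level amplitudes as a separate analysis, since the group mean vector shrinks with phase scatter under either model.

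The cost is analysis wording and modest programming, with no new data. Intervals for sex and age will be wider.
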